## Abstract

**Introduction:**

Sexually transmitted infections (STI) are a major public health problem. Condoms provide effective protection but there are many barriers to use. Face-to-face health promotion interventions are resource-intensive and show mixed results. Interactive digital interventions may provide a suitable alternative, allowing private access to personally tailored behaviour change support. We have developed an interactive digital intervention (the Men's Safer Sex (MenSS) website) which aims to increase condom use in men. We describe the protocol for a pilot trial to assess the feasibility of a full-scale randomised controlled trial of the MenSS website in addition to usual sexual health clinical care.

**Methods and analysis:**

Participants: Men aged 16 or over who report female sexual partners and recent unprotected sex or suspected acute STI. Participants (N=166) will be enrolled using a tablet computer in clinic waiting rooms. All trial procedures will be online, that is, eligibility checks; study consent; trial registration; automated random allocation; and data submission. At baseline and at 3, 6 and 12 months, an online questionnaire will assess condom use, self-reported STI diagnoses, and mediators of condom use (eg, knowledge, intention). Reminders will be by email and mobile phone. The primary outcome is condom use, measured at 3 months. STI rates will be recorded from sexual health clinic medical records at 12 months. The feasibility of a cost-effectiveness analysis will be assessed, to calculate incremental cost per STI prevented (Chlamydia or Gonorrhoea), from the NHS perspective.

**Ethics and dissemination:**

Ethical approval: City and East NHS Research Ethics Committee (reference number 13 LO 1801). Findings will be made available through publication in peer-reviewed journals, and to participants and members of the public via Twitter and from the University College London eHealth Unit website. Raw data will be made available on request.

**Trial registration number:**

Current Controlled Trials. ISRCTN18649610. Registered 15 October 2013 http://www.controlled-trials.com/ISRCTN18649610.

## Introduction

### Men's sexual health

Sexually transmitted infections (STI) are a major public health problem, with high social and economic costs.^1^
^2^ Condoms are effective for prevention of STI; however, there are many barriers to successful use, for example, decrease in sensation, interruption of sex, incorrect size or fit, use of alcohol/recreational drugs, anxiety affecting sexual performance, and stigma associated with carrying condoms.^3^
^4^ The prevention of pregnancy is often a stronger motivation for condom use than prevention of STI.^5^ Condoms may be perceived as a barrier to intimacy and trust,^4^ and use is often lower in established relationships.^6^

Since it is men who primarily experience many of the disadvantages of using male condoms (eg, reduced pleasure), and have the power to influence condom use for penetrative sex (since they wear condoms), prevention efforts are needed to target the obstacles to condom use that men face.^3^ While there are a variety of health promotion interventions aimed at improving sexual health for men who have sex with men (MSM), there are fewer interventions specifically for adult men who have sex with women (MSW),^7^
^8^ despite the fact that MSW report much less consistent condom use than MSM.^9^ Men are less likely than women to visit health professionals and generally have shorter clinic appointments,^10^
^11^ so they may be less likely to be offered health promotional advice or risk reduction counselling in the context of routine appointments. Men may be reluctant to discuss their sexual health with health professionals, partners or friends.^12^ An online intervention therefore offers an alternative avenue to reach men.^13^

### Sexual health interventions

Guidance from the National Institute for Health and Care Excellence recommends that people at high risk of STI are offered one-to-one structured discussions to address risk-taking,^1^ and this is increasingly being offered as part of routine care in genitourinary medicine and other healthcare settings. While interventions such as motivational interviewing can impact on sexual behaviour,^1^ in practice it is resource-intensive to train and support staff, and difficult to find time for structured discussions in busy clinical services. A potential alternative to such interventions is the use of interactive digital interventions (IDI).

We define IDI as ‘Computer-based programmes that provide information and one or more of decision support, behaviour change support, or emotional support for health issues’.^13^ IDI require contributions from users to produce personally relevant tailored material and feedback. IDI are highly suitable for sexual health promotion because access can be private, anonymous and self-paced,^14^ which may be particularly important for men who may be reluctant to disclose a lack of knowledge or skill. Interventions can be targeted for specific groups (eg, by age, gender or sexuality), and content can be tailored for individuals.^15^ IDI can be expensive to develop but offer the advantages of intervention fidelity^16^ and the potential to reach large audiences at relatively low dissemination costs.

IDI can improve sexual behaviour (including condom use),^13^
^17^ as well as increasing knowledge, self-efficacy and safer sex intention.^13^
^18^ More evidence is needed to establish effects on biological outcomes (STI) and cost-effectiveness. The Men's Safer Sex (MenSS) website is an IDI which aims to increase condom use and reduce STI in men attending sexual health clinics. The present pilot trial aims to determine the optimum parameters of a full-scale randomised controlled trial (RCT) to assess the efficacy of the MenSS website intervention.

## Objectives

To establish the feasibility and optimal design of a full-scale RCT to test the effect on condom use and STI acquisition of the MenSS intervention website for men attending sexual health clinics:
Conduct a pilot trial to optimise the parameters for a phase III RCT of usual clinical care plus the IDI compared to usual clinical care only, using the primary outcome of self-reported condom use at 3-month follow-up.Optimise the data collection and analysis procedures for a health economic analysis for a future Phase III RCT.

### Methods and analysis

The pilot trial will be a phase II proof of concept RCT to evaluate the effect of the MenSS IDI on increasing condom use in addition to usual clinic care for men in sexual health clinics.

### Setting

Participants will be recruited from three sexual health clinics: The Homerton Hospital Department of Sexual Health, St Bartholomew's Sexual Health Centre, and City of Coventry Health Centre Integrated Sexual Health Services Department. These clinics serve a diverse range of patients in terms of age, socioeconomic status and ethnicity.

### The intervention

The MenSS website content and design was developed based on evidence from the sexual health research literature and theories of behaviour change, qualitative interviews with men in sexual health clinics, and discussions with clinical and academic experts in sexual health and digital technologies.^19^ The development process was iterative, with a high level of user involvement. The intervention is designed to be delivered initially in clinic, to make use of the time when patients are waiting to be seen, but also providing (and encouraging) online access after patients have left the clinic.

The MenSS intervention consists of an interactive website. While in clinic, users will be presented with a tailored package of website content which addresses individual men's barriers to condom use. The site targets a number of influences on effective condom use, such as:
Condom knowledge (eg, about sizes and types of condoms);Condom use skills;Difficulties in negotiating condom use;Inaccurate beliefs about STI risk;Social influences, such as perceived/expected partner response;Sexual pleasure;Being caught in the ‘heat of the moment’;Alcohol and drug use.

While in clinic, users will be asked to select their own personal barriers to condom use. This task will produce a tailored package of information, offering solutions or counter-arguments to barriers (including interactive activities and quizzes, videos and case vignettes), which will be presented prominently on the homepage. Some content is presented to all users (eg, training in condom use skills), and all content will be available via website navigation tabs. Participants will be led through their tailored content package sequentially, and will be asked to set goals to change their behaviour. If wanted, participants will receive emails to assess achievement of goals, and to encourage them to visit the intervention website again.

### Procedure

Participant recruitment is designed to be self-directed, using a touch screen tablet computer, which will be available in the clinic waiting room. Participants will be directed to the tablet computer via brief information leaflets and posters in the waiting room, or by clinic staff. The trial software is set up to allow participants to be led through the steps of screening, consent, automatic randomisation, data collection and intervention viewing, without assistance from clinic staff (figure 1). A member of the study team or the sexual health clinic research staff will be present if needed to provide technical assistance and to answer questions about the study.

**Figure 1 BMJOPEN2014007552F1:**
[figure not shown]
Men's Safer Sex trial software framework: online study information, consent, registration, data collection and randomisation.

#### Online eligibility, consent, registration, randomisation, data collection

The tablet computer in the clinic waiting room will present information about the trial and an invitation to participate. Potential participants will then be asked to complete a screening questionnaire to determine their eligibility for the trial. Those who are ineligible at this point will be informed of this, and thanked for their time. Those who are eligible will receive detailed information regarding the study. Participants will be asked to give informed consent by agreeing to a number of statements (see online supplementary appendix 1: online participant information and consent). They will then be asked to give their contact details (email address and telephone number), in order to contact them for follow-up assessments, to send them reminders to view the website, to remind them that they are participating in the trial, and to send an electronic shopping voucher to recompense participants for their time. Participants will also be asked to create a password. The password will give the intervention group access to the intervention website, which will also enable collection of website usage data. It will also be needed to access the follow-up questionnaires. Demographic and baseline sexual health data will then be collected. At this point, the software program will use a computer algorithm to randomly allocate participants to either the intervention or control conditions. This allocation will be unalterable.

#### Follow-up data collection

At 3, 6 and 12 months after their initial clinic visit, participants will receive an automated email asking them to complete a follow-up questionnaire (see Outcome assessment section), by clicking on a weblink to an online questionnaire. If they do not complete the questionnaire, they will receive three further email prompts, at 1-week intervals, as well as two text messages to their mobile phone (again including the weblink) alongside the latter two emails. If participants still do not respond, the researcher will telephone participants a week after the final email to remind them to fill in the study questionnaire. Information about STI diagnoses will be collected at all time points via self-report, and at 12 months by recording diagnoses or suspected diagnoses over the past year recorded in the clinical notes at the sexual health clinics participants are recruited from.

### Inclusion and exclusion criteria

#### Inclusion criteria

Men aged 16 years and above (with no upper age limit); able to read English; with access to the internet; and at high risk of future STI (ie, two or more partners in the past year (male or female) and some non-condom use in the past 3 months; or symptoms of acute STI; or seeking treatment for an STI); and for whom at least half of their sexual partners are female.

#### Exclusion criteria

HIV-positive men and men with hepatitis B or C will be excluded, since patients with these diagnoses are likely to receive risk reduction advice in the course of routine clinical care. We will exclude men who have had sexual experience only ever with males, more often with males but at least once with a female, or no sexual experience at all.^20^

### Randomisation

Once participants have been checked for eligibility, given informed consent, and submitted baseline data, they will be allocated by the computer algorithm randomisation system to either the intervention or control group. The participant will be informed with an automated message on the tablet computer, and this allocation will be unalterable.

### Allocation concealment

Allocation will be undertaken using a concealed automated computer-based algorithm, which will be immediate.

Participants allocated to the control condition will be notified that they have not been selected to view the intervention and told that they will be contacted again in 3, 6 and 12 months to gather follow-up data. Those allocated to the intervention condition will be directed to the intervention website where they will be presented with a tailored package of health promotion/behaviour change content. Website usage (page views) will be automatically recorded.

### Outcome assessment

#### Development of the online measurement instrument

We adapted the Sexunzipped online sexual health questionnaire^21^ to measure outcomes and mediators of condom use. We selected items for inclusion based on a literature search for established measures, and consultation with experts. We conducted interviews with men in sexual health clinics (N=11) to gain feedback on successive versions of the outcome questionnaire. Interviews with men checked their understanding of questions, the clarity of questions, and content suitability for the selected measures of behavioural outcomes and mediators of those outcomes. On the basis of feedback, we modified the structure and content of the outcome questionnaire.

Mediators of behaviour change (eg, beliefs about pleasure, motivation, knowledge, self-efficacy), behavioural outcomes (including condom use, STI testing, communication with partner/s) and cumulative STI incidence (self-reported and from clinical notes) will be measured. Service use and quality of life will be measured for the cost-effectiveness analysis. The primary outcome will be self-reported condom use at 3-month follow-up.

#### Measures

In the light of evidence that measurement alone may prompt behaviour change,^22^ we will measure a limited number of outcomes (condom use and the main mediators, and self-reported STI diagnoses) at baseline; we will also assess a full range of outcomes at 3, 6 and 12 months (table 1). All assessments have a recall period of the previous 3 months, which is the time between follow-up assessments.

**Table 1 BMJOPEN2014007552TB1:** Variables assessed at each time point

Baseline measures	3-month, 6-month and 12-month follow-up assessments
Demographic details (age, occupation, ethnicity)	

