##### STI diagnoses

Participants will be asked to report STI diagnoses over the past 3 months at every follow-up point. We will also assess whether participants have received treatment due to a partner being diagnosed with an STI. In order to assess laboratory diagnoses, all STI diagnoses recorded in sexual health clinic records (in the participating sites) over the study period will be noted at 12 months.

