##### Communication with partners

To assess communication with partners over a 3-month period, we adapted the six-item Partner Communication Scale.^29^ The scale was adapted in the light of qualitative fieldwork, and the recall period was modified from 6 to 3 months, as follow-up assessments will be 3 months apart.

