### Cost-effectiveness analysis

The principal aim of the economic data collection will be to determine the feasibility and validity of collecting cost and outcome data for a cost-effectiveness analysis within a phase III trial. We will conduct an initial cost-effectiveness analysis (CEA) of incremental cost per gain in outcome, looking at the cost per STI prevented (*Chlamydia* or *Gonorrhoea*), comparing intervention participants with controls from the NHS perspective. This will include one-way, two-way and parametric sensitivity tests.

The aim of the analysis will primarily be to evaluate whether information collected is fit for the purpose, and to inform information collection in a future trial. We will examine the feasibility of collecting cost data for intervention and control participants including costs associated with STI tests and treatments, and contract tracing, testing and treatment. Trial subjects may access sexual health services from a range of providers, so information from sexual health clinic notes alone may prove unreliable. We will therefore ask participants about sexual health-related health service contacts over the past 12 months as part of the self-reported outcomes. Information collected from sexual health clinic notes will be used to assess the reliability of the self-reported information collected. Personal Social Services Research Unit (PSSRU) reference costs,^34^ British National Formulary^35^ and other national sources of costing information will be used to calculate unit costs. Costs associated with the maintenance of the intervention website and updating the website will also be included.

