STIs prevented will be calculated by taking account of diagnoses recorded from clinical records at 12-month follow-up as well as self-reported episodes for the previous year. We will calculate the cost per episode of *Chlamydia* or *Gonorrhoea* prevented for the intervention group versus controls. The National Institute of Health and Care Excellence (NICE) recommends that quality-adjusted life years (QALYs) are used as the outcome in CEA, to allow for the comparison of results for different CEA across disease areas. QALYs are calculated by multiplying HRQoL by the amount of time spent in the HRQoL state. The EQ-5D is the questionnaire recommended by NICE to calculate HRQoL;^24^ it has been recognised, however, that the EQ-5D may not be suitable for economic evaluations of public health interventions as it may not capture the relevant information on the full psychosocial impact of public health interventions or be sufficiently sensitive for that purpose.^36^
^37^ We will therefore also collect data on the performance of the Sexual QoL questionnaire^25^ to assess its suitability for use in a future large-scale RCT.

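### Three-month recall is justified by three-month spacing, but the last gap is six months, so self-reported STIs miss months 6–9 of the year that the economic analysis needs

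*Protocol article*

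**What the plan says.** The Measures section fixes one recall period and gives a reason for it: "All assessments have a recall period of the previous 3 months, which is the time between follow-up assessments". The section on communication with partners repeats the reason, shortening a published scale's recall from 6 to 3 months "as follow-up assessments will be 3 months apart". The section on follow-up data collection sets the schedule: "At 3, 6 and 12 months after their initial clinic visit, participants will receive an automated email asking them to complete a follow-up questionnaire".

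For infections, the STI diagnoses section applies the same window: "Participants will be asked to report STI diagnoses over the past 3 months at every follow-up point". Diagnoses in the clinic records of the participating sites are read once, at 12 months, for the whole study period.

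Two places need more than this. The section on developing the measurement instrument says "cumulative STI incidence (self-reported and from clinical notes) will be measured". The Cost-effectiveness analysis section builds STIs prevented from the 12-month clinic records "as well as self-reported episodes for the previous year".

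Service use is treated differently. The Service use section sets the window as the study period, and the Cost-effectiveness analysis section says: "We will therefore ask participants about sexual health-related health service contacts over the past 12 months as part of the self-reported outcomes".

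**The concern.** The reason given for the recall period does not match the visit schedule, and the mismatch falls on a quantity that the analysis uses. A man who answers every questionnaire is still never asked about STI diagnoses in months 6–9, yet the economic analysis treats a full year of self-reported episodes as available.

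Self-report is the article's own remedy for a weakness in the clinic records. It says that men may use several providers, so notes from the recruiting clinics may be unreliable on their own. The gap therefore sits in the source meant to fill the holes in the other.

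Optimising data collection for the health economic analysis is one of the two stated objectives, so a built-in hole in the effect measure bears on what the pilot is meant to test. The article also plans to use clinic notes to check the reliability of self-report. If STI diagnoses are compared in this way, 12 months of notes set against 9 months of self-report would show disagreement caused by the questionnaire rather than by the respondents.

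**Working it through.** **Inputs.** Assessments at 0, 3, 6 and 12 months (Follow-up data collection, with baseline as 0). STI recall of 3 months at each follow-up (STI diagnoses). Self-reported STI window needed: 12 months (Cost-effectiveness analysis). Clinic-note window: 12 months, participating sites only (Follow-up data collection; STI diagnoses).

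**Step 1: the stated spacing.** The article gives the time between follow-up assessments as 3 months. The gaps are 3 − 0 = 3, 6 − 3 = 3 and 12 − 6 = 6 months. The stated figure holds for the first two intervals and fails for the third.

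**Step 2: months covered by self-report.** Each window runs from (visit − recall) to the visit.

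| Follow-up | Window with 3-month recall | Window if the 12-month item recalls 6 months |
|---|---|---|
| 3 months | 0–3 | 0–3 |
| 6 months | 3–6 | 3–6 |
| 12 months | 9–12 | 6–12 |
| Total covered | 9 of 12 months (75%) | 12 of 12 months |

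With 3-month recall throughout, months 6–9 are uncovered: 3/12 = 25% of the year.

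**Step 3: what is lost once clinic notes are added.** Let f be the share of diagnoses made outside the participating sites. The documents give no figure, so f is an assumption shown over its range. Assume also that:
- events, and the difference between arms, accrue at a constant rate over the year;
- f is the same in both arms;
- notes capture every diagnosis at participating sites, and self-report captures every diagnosis inside its windows;
- costs cover the full 12 months.

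Diagnoses at participating sites, share (1 − f), are counted for all 12 months. Diagnoses elsewhere, share f, are counted for 9 of 12 months.

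Fraction of STIs prevented that is counted = (1 − f) + 0.75f = 1 − 0.25f.

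Inflation of cost per STI prevented = 1/(1 − 0.25f).

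| f (assumed) | Shortfall in STIs prevented, 0.25f | Inflation of cost per STI prevented |
|---|---|---|
| 0 | 0% | 1.00 |
| 0.2 | 5% | 1/0.95 = 1.05 |
| 0.5 | 12.5% | 1/0.875 = 1.14 |
| 1 | 25% | 1/0.75 = 1.33 |

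Under these assumptions both arms lose the same fraction, so a ratio of STI rates is not biased. The absolute number prevented, which is the denominator of the cost-effectiveness ratio, is.

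**Step 4: service use.** The Measures section applies 3 months to every assessment. The Service use section says the study period, and the Cost-effectiveness analysis section says 12 months. These cannot all be right. If the 12-month wording governs, costs span 12 months and self-reported infections span 9. If the Measures sentence governs, self-reported service use has the same gap in months 6–9.

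**The case against.** The strongest reply is that STIs have two sources. Clinic notes cover the full year, and the economic analysis combines both, so a diagnosis in months 6–9 at a participating site is still counted. This stands, and it is why the effect is a range from 0 to 25% that depends on f. A reader might infer that a quarter of all STI incidence is missing, or that cost per STI prevented is inflated 1.33-fold. That is the extreme at which every diagnosis is made elsewhere, and nothing in the documents supports it. The constant-rate assumption may also be generous: the Condom use section expects most behaviour change soon after recruitment, so months 6–9 may hold less than a quarter of any difference between arms.

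A reader might also infer that 12-month cost totals cannot be built. The documents do not support this, because the Cost-effectiveness analysis section gives service contacts a 12-month recall. What remains is a conflict of wording with the Measures section. Nor is there a pregnancy finding: that item asks about 3 months, and no 12-month pregnancy total is promised.

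The instrument itself is in online supplementary appendix 2, which is not shown. A longer-recall STI item at 12 months may exist, and the sentence in Measures may simply be too broad. That limits what can be said about the questionnaire. It does not remove the contradiction in the article, where the STI section explicitly sets 3 months at every follow-up.

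Finally, this is a pilot with an initial economic analysis, and no decision rule in the article rests on its cost per STI prevented. That is fair, and it limits the harm. But judging whether the economic data are fit for use in a later trial is the declared aim of that analysis, so a known gap should not be carried into it.

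**Conclusion.** The concern holds in this form. The 3-month recall is justified by a spacing that is wrong for the interval from 6 to 12 months. As described, self-reported STI diagnoses cover 9 of 12 months and cannot supply the cumulative self-reported incidence or the year of self-reported episodes that the article uses. What is actually lost is diagnoses made outside the participating sites in months 6–9.

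The resulting understatement of STIs prevented is 0.25f, with cost per STI prevented inflated by 1/(1 − 0.25f). This rests on a constant event rate, on f being equal in the two arms, and on full-year costs; f itself is unknown from the documents. The separate conflict over service-use recall needs reconciling, but it does not show that cost data are missing.

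The primary outcome is unaffected, because its 3-month recall at the 3-month follow-up matches the interval exactly.

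**What to change.** - At 12 months, ask about STI diagnoses, and about treatment because of a partner's STI, since the 6-month assessment, or since the last completed questionnaire if the 6-month one was missed.
- Keep 3-month recall for condom-use counts and the scales, so that they stay comparable across time points.
- Correct the rationale in Measures and in Communication with partners: the spacing is 3, 3 and 6 months.
- Make Measures, STI diagnoses, Service use and Cost-effectiveness analysis state the same recall for each item, and check them against the questionnaire in appendix 2.

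The cost is rewording a few online items at one time point. The downside is slightly longer recall, at that time point only, for events that are fairly memorable. If the 12-month questionnaires have already been completed with 3-month wording, the missing window can be recovered only by contacting participants again. Failing that, the report should say that self-reported STIs cover 9 of 12 months and show cost per STI prevented over a range of f.
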